This paper describes the protocol for a cluster-randomized controlled trial (CRCT) to test an enhanced linkage to care intervention during HBHCT in rural Uganda. Our Providing Access To HIV care (Providing Access to HIV Care (PATH)/ *Ekkub*o) intervention enhances a similar strategy tested by Coates, Wanyenze, Bangsberg, and colleagues [39] that was found to reduce time to HIV care and treatment among patients receiving opt-out HIV testing in health facilities in Uganda. The intervention facilitated linkage by: providing orientation to the HIV care system, counseling to help clients identify and reduce barriers to engagement in care, and assistance disclosing and identifying a treatment supporter. The PATH/Ekkubo intervention described in this paper enhances the original intervention in order to increase its impact on multiple outcomes, including HIV viral suppression, and adapts the intervention to address barriers specific to HBHCT by providing additional counseling with increased emphasis on HIV stigma reduction through increased social support. We test this intervention in a CRCT, with randomization at the level of the village rather than at individual level, to avoid potential contamination since village residents interact with one another regularly in our study setting. The specific aims are:Compare the efficacy of the enhanced linkage to care intervention (PATH) vs. standard-of-care (paper-based referrals) at achieving individual and population-level HIV viral suppression, and intermediate outcomes of linkage/time to care, time to/receipt of ART. We hypothesize that the PATH intervention study arm will have a higher proportion of participants who are: a) virally suppressed at 12-month follow up, and will have shorter time to: b) HIV care and c) ART initiation, among those eligible, than the standard-of-care study arm. We also hypothesize that the effect of the intervention on HIV viral suppression will be mediated by intermediate behavioral outcomes: linkage to care and ART initiation. Finally, at the cluster level, we hypothesize that villages randomized to the intervention arm will have higher rates of population-level HIV viral suppression than those in the standard-of-care study arm at 12-month follow-up.Using the standard-of-care group as a natural history control, collect longitudinal data on barriers to and facilitators of linkage to and retention in care and treatment and HIV viral suppression.Estimate the cost and cost-effectiveness of the intervention, as compared to standard-of-care HBHCT, in terms of: viral suppression, linkage to care, and receipt of ART.

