##### Intervention trial

Individuals who participated in the brief baseline questionnaire interview and are identified as newly diagnosed HIV positive by our HBHCT team, as well as individuals who disclose as being known to be HIV positive during the baseline questionnaire and are confirmed positive in re-testing by the HBHCT team, but have never linked to HIV care, will be eligible for participation in the intervention trial. Only one person per household will be included in the intervention trial to ensure independence in the data. Using computerized random selection, we will randomly select one of the eligible HIV-positive household members for inclusion in the intervention trial. For ethical reasons the same follow-up support (intervention or control) will be offered to other newly diagnosed or HIV-positive household members not in care as will be provided to the household member included in the intervention study. A total of approximately 600 participants (approximately 300 in intervention and 300 in control arm villages) who are eligible and provide written informed consent to participate in the intervention trial will be enrolled.

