#### Independent variables

*Sociodemographics* (baseline). We will assess participants’ gender, age, tribe, educational level, socioeconomic status, employment status, income, religion, gender, marital/partnership status, distance to clinic, and travel time to the clinic.
*Prior use of health services* (baseline). We will measure prior use of HIV services, including history of HIV testing, frequency, location, and reasons for health service use in the prior 6 months, male circumcision for men, and location of births for women.
*CD4 cell count* (baseline, 12 months)*.* CD4 cell count will be assessed via venous blood draws along with VL at baseline and 12-month follow-up. Baseline CD4 values may affect viral suppression success [47]. We did not include CD4 as an outcome measure because according to recommendations by WHO and the United States Department of Health and Human Services, when VL is available, CD4 has little added value for monitoring treatment adherence and efficacy of ART [44, 48].
*Tuberculosis (TB)* (six and 12 months, clinic records). We will assess co-infection with TB using questions adapted from the MOH’s HIV clinic card. Interviewers will use the participant’s clinic card and self-report to record if the participant is TB infected, date of diagnosis, and treatment initiation and regimen.
*ART adherence* (six and 12 months). We will assess self-reported adherence to ART using the Adult AIDS Clinical Trials Group scale [49], which includes recall questions about ARVs missed for the previous 4 days prior to the interview, as well as 17 items assessing participants’ main barriers to adherence. It has demonstrated construct validity in Uganda and similar settings [50].
*Disclosure of HIV-test results* (six and 12 months). We will measure HIV status disclosure with an instrument used in prior research in Uganda and other African countries [39, 51]. It asks about the disclosure of serostatus to spouses, sexual partners, family members, community members/leaders, physicians, etc. The proportion of participants reporting each disclosure is calculated after eliminating those who say the disclosure was not applicable to them.

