*Receipt of instrumental and emotional social support* (six and 12 months). We will measure receipt of instrumental and emotional social support using the Social Support Scale [51], which contains six items on emotional support and four items on instrumental social support. This scale was adapted from the Duke-University of North Carolina Functional Social Support Questionnaire [52] and has been validated among PLHIV in rural Rwanda (α = 0.91) [53]. In addition, we will determine if participants have a treatment supporter, have attended HIV support groups, or been counseled by an HIV-positive peer educator, and how helpful each of these forms of counseling have been on a four point scale ranging from “not helpful” to “very helpful.”
*HIV stigma* (baseline, six, and 12 months). At baseline, for those individuals reporting they are HIV negative or do not know their HIV status, we will measure enacted stigma, including nine items on discrimination, stereotypes, and prejudice using Kalichman et al.’s [54] AIDS-related stigma scale, which has been validated in South Africa [54]. We will also measure anticipated stigma, asking participants how they would feel if they tested positive, using six items from Earnshaw’s [42] anticipated stigma scale and six items from Berger et al.’s [55] HIV stigma scale. We will calculate the mean of all participants from each village to get a village (cluster)-level HIV stigma score at baseline. At six and 12-month follow up, and at baseline for those who report already knowing they are HIV positive, we will assess the following dimensions of HIV stigma among PLHIV [56]: (a) anticipated stigma using six items from Earnshaw’s [42] anticipated stigma scale and two subscales from Berger et al.’s [55] HIV stigma scale: eight items assessing anticipated stigma related to disclosure and eight items assessing anticipated stigma related to concern with public attitudes about PLHIV; (b) enacted stigma using six items from Earnshaw’s scale [42], 16 items from the personalized HIV stigma subscale of Berger et al.’s [55] scale, as well as items from Sayles et al.’s [57] multidimensional HIV stigma scale: 12 items from the stereotypes subscale and seven items from the social relationships subscale; and (c) internalized stigma using Kalichman et al.’s [58] internalized AIDS-related stigma scale. All of these measures have shown good reliability among sub-Saharan African samples (α = 0.73-0.78) [59–61].

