*Subjective health status* (six and 12 months). We will use the 36-item Medical Outcomes Study-HIV short form [62] to assess subjective health status adapted for the Ugandan context [63] and shown to be reliable among PLHIV in rural populations in Uganda (α > 0.70) [63, 64].
*Perceived need for HIV care/treatment* (six and 12 months). We will adapt five items used in a study in Zambia [65] to assess participants’ perceived need for HIV treatment. The items assess participants’ agreement with statements such as: “You do not need to go to the HIV clinic because you feel healthy” and “You do not want to take any medicine.”
*Barriers to care* (six and 12 months). We will measure barriers to attending HIV care, including distance/time to the clinic, financial barriers, work/child care responsibilities, wait times, and concerns with privacy among health workers. We will include 18 items adapted from the LifeWindows Information Motivation Behavioral Skills ART Adherence Questionnaire [66] and Smith et al.’s [67] scale on engagement and retention in pre-ART HIV care. We will also determine the actual distance and travel time from the participants’ home to the HIV clinic and for the cost of transportation to the clinic, for those who are able to pay.
*HIV care system literacy.* We will use nine items from the Brief Estimate of Health Knowledge and Action HIV Version scale [68] to assess participants’ knowledge of the HIV care system, including questions on where they can get treatment, the cost of treatment, treatment eligibility, etc.
*Beliefs about traditional and western medicine* (six and 12 months). We will assess beliefs towards western and traditional medicine and use of traditional medicine to treat HIV using items adapted from the treatment denialism subscale of Kalichman’s AIDS denialism scale [69].
*Relationship with the clinic provider*. We will measure participants’ satisfaction with their healthcare provider using 10 items from a scale used in South Africa by Westaway and colleagues [70].
*Acceptance of HIV diagnosis.* Three items modified from the Brief COPE Scale [71] will be used to assess participant’s acceptance of their HIV diagnosis by asking participants if they have refused to believe their test results since they tested positive.
*Alcohol use*. We will assess alcohol use using the Alcohol Use Disorders Identification Test [72], shown reliable among PLHIV in rural Uganda (α = 0.71) [73].

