### Data analysis approach

Univariate statistics will be conducted on primary and secondary endpoints as well as covariates to describe the sample characteristics for the two study arms. Attrition in the two arms will be compared. Multiple imputation technique will be implemented and sensitivity analysis will be conducted.

To assess the primary outcome (the proportion of participants who are virally suppressed at 12-months) and secondary outcomes (linkage to care, time to care, receipt of opportunistic infection prophylaxis, and initiation of ART among those eligible for ART at baseline), linear mixed models and nonlinear mixed models will be applied. Information criterion such as Akaike information criterion or Bayesian information criterion will be used for model selection.

In evaluating the intervention effectiveness mechanisms, and mediators and moderators, we will use structural equation modeling to estimate the causal effects using growth mixture modeling to account for the longitudinal and clustered data. To assess an existence of moderators of an intervention effect, covariates such as disclosure, social support, HIV stigma, adherence, distance from the clinic, CD4 count, having other HIV-positive household members, number and duration of intervention sessions received, village-level stigma towards PLHIV, etc. will be included. A nonlinear mixed model will be fitted independently for each covariate plus the treatment variable and an interaction term between the covariate and the treatment.

To examine the natural history of stages in the HIV care continuum, we will use the control group to identify barriers to and facilitators of linkage to care and treatment, retention, and viral suppression, potential predictors include: sociodemographics, HIV stigma, disclosure, etc. Stepwise forward selection method from both logistic regression model and general linear model will be used to identify potential significant predictors for our analyses. Predictors that are selected from the stepwise method will be included in our mixed models.

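### Aim 2 may report correlates or consequences of linkage as its barriers or facilitators: disclosure is first measured at six months, and the stepwise selection step names no village term

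*Protocol article*

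**What the plan says.** All references are to the Protocol article.

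- **Purpose (Background, aims).** The second aim reads: "Using the standard-of-care group as a natural history control, collect longitudinal data on barriers to and facilitators of linkage to and retention in care". The control arm holds half of the trial (Intervention trial: "approximately 300 in intervention and 300 in control arm villages").
- **Selection (Data analysis approach).** "Stepwise forward selection method from both logistic regression model and general linear model will be used to identify potential significant predictors for our analyses". The next sentence reads: "Predictors that are selected from the stepwise method will be included in our mixed models". On candidates: "potential predictors include: sociodemographics, HIV stigma, disclosure, etc". The outcomes covered are linkage to care and treatment, retention, and viral suppression.
- **Timing of candidates (Independent variables; Table 3).** Disclosure: "Disclosure of HIV-test results* (six and 12 months". Social support: "six and 12 months). We will measure receipt of instrumental and emotional social support using the Social Support Scale". Barriers: "six and 12 months). We will measure barriers to attending HIV care, including distance/time to the clinic". None of these three has a baseline value. Sociodemographics (with distance and travel time to the clinic), prior service use, CD4 count and a form of the stigma measure are collected at baseline.
- **Timing of the outcome (Secondary outcome measures).** Linkage is timed from the HIV test to enrolment at an HIV clinic.

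**The concern.** The method and the measurement schedule do not fit together for the linkage outcome. A person who enrols at a clinic in month two and is interviewed in month six reports disclosure, support and barriers as they stand after four months in care. Being in care can move these measures directly. The disclosure instrument counts disclosure to physicians. The support measures include attending HIV support groups, and the Setting section places peer support groups at district hospitals and level III health centres. No rule limits linkage predictors to values recorded before linkage.

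There is a second, smaller problem. Variables are screened in ordinary logistic and general linear models that name no village effect, and clustering enters only when the survivors are refitted. The refit adjusts standard errors for clustering. It does not reconsider which variables were let in, and it does nothing about time order.

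At stake is the use of Aim 2. The Discussion intends these data to inform follow-up and support in home-based testing. A finding that disclosure facilitates linkage could not be told apart from linkage leading to disclosure.

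**Working it through.** The article gives no figure for Aim 2 to reproduce, so the check sizes the two problems from its other figures. Assumptions are marked.

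**1. How much linkage precedes the six-month interview?** The article does not say. Background cites one Ugandan study with 58% linked within 12 months, and a range of 42% to 97% within 1 to 12 months across studies. Assume a constant hazard:

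- λ = −ln(1 − 0.58)/12 = 0.0723 per month
- linked by six months = 1 − exp(−6 × 0.0723) = 0.352
- share of 12-month linkage that comes earlier = 0.352/0.58 = 0.61

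In general the share is 1/(1 + √(1 − p)). If the cited range is treated as 12-month figures (assumed), p = 0.42 gives 57% and p = 0.97 gives 85%. Under a constant hazard the share always exceeds one half; a rising hazard could bring it lower.

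**2. What does that do to selection?** Simulation with n = 300 × 0.82 = 246 (control arm less the planned 18% attrition), 58% linked, and a binary six-month predictor with no effect on linkage and 50% prevalence (assumed). Linkage before the interview raises its prevalence by 10 or 20 points (assumed). Selection is at p < 0.05, with 1,000 runs per setting.

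| Share of linkage before interview | Selected, 10-point rise | OR | Selected, 20-point rise | OR |
|---|---|---|---|---|
| 0% | 4.5% | 0.99 | 5.4% | 1.00 |
| 25% | 5.9% | 1.10 | 12.7% | 1.23 |
| 50% | 11.9% | 1.24 | 36.1% | 1.51 |
| 75% | 23.6% | 1.38 | 64.2% | 1.85 |
| 100% | 31.4% | 1.48 | 87.7% | 2.33 |

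When the predictor is always measured before linkage (first row), the rate is the nominal 5%.

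**3. What does omitting village from selection do?** The coefficient of variation k = 0.24 comes from Sample size justification and power analysis. It was set for viral suppression and is borrowed here for linkage (assumed).

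- ICC = k²p/(1 − p): 0.0576 × 0.55/0.45 = 0.070 at p = 0.55; 0.0576 × 0.58/0.42 = 0.080 at p = 0.58
- Cluster size m: 14 × 0.82 = 11.5 after attrition, up to 600/40 = 15 before it
- Design effect for a village-level predictor = 1 + (m − 1) × ICC: 1.74 (m = 11.5, p = 0.55) to 2.11 (m = 15, p = 0.58)
- Actual error rate = 2(1 − Φ(1.96/√DEFF)): 13.7% to 17.8%

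Simulating an ordinary logistic model in 20 villages of 12 (2,000 runs) gives 14.5% for a village-level predictor. For individual-level predictors with within-village correlation 0, 0.1 and 0.3 (assumed), it gives 4.8%, 5.6% and 8.1%.

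**The case against.** The strongest reply has five parts.

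- **The candidate list is mixed.** Of the three candidates named, sociodemographics and stigma have baseline measures. Only disclosure does not; support and barriers are read into an open-ended list. This stands, and it narrows the point to disclosure plus other plausible candidates. For newly diagnosed people, however, the baseline stigma items are anticipatory and differ from the scales used at follow-up.
- **Some outcomes come later.** Six-month measures can properly precede 12-month suppression. This stands; the time-order problem concerns linkage and ART initiation.
- **Villages are not ignored.** A reader might infer that the analysis disregards clustering. The article does not support that, because selected predictors enter mixed models. Only the selection step lacks a village term, and for individual-level candidates the effect is small. The one explicit village-level covariate, the village stigma score, is listed with the moderators and not for this aim.
- **The text does not speak of causes.** A reader might infer that consequences of linkage will be presented as its causes. For this aim the article speaks of predictors, barriers and facilitators. Those words still imply a direction that six-month data cannot give for early linkers.
- **Time-ordering rules belong in the analysis plan.** A condensed article may leave them out. But here it states the selection method, names disclosure as a candidate and fixes the measurement times. Followed as written, these allow the problem.

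**Conclusion.** The point holds for Aim 2, at moderate weight; the randomised comparison is untouched. As written, a variable recorded after linkage can be selected as a predictor of it, so correlates or consequences of linkage may be reported as barriers or facilitators.

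The size depends on two unknowns: the share linking before six months and how far linkage shifts the measure. If half to three-quarters of linkage comes first, a null predictor is selected 12–24% of the time with a 10-point shift and 36–64% with a 20-point shift. A reader might infer that most linkage will certainly have happened by six months. That is plausible, but the article gives no such share; the 61% rests on a constant hazard.

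Leaving village out of selection matters mainly if village-level candidates are used (about 14–18% against a nominal 5%, with an ICC borrowed from suppression). For individual-level candidates it is about 5–8%.

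**What to change.** Reword the Aim 2 paragraph of Data analysis approach:

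1. For linkage and ART initiation, take predictors measured at baseline.
2. Use six-month measures in a landmark analysis of those not yet linked (or not yet on ART) at six months, with events counted from six to 12 months, or as predictors of 12-month suppression. Elsewhere, report them as correlates.
3. Include the village random effect in the selection step, and label the selected results exploratory.

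Replacing stepwise selection with a pre-specified set or penalised regression is a matter of preference and is not needed to meet this point.

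**Cost.** No new data are needed. The landmark analysis has fewer events: under the constant-hazard assumption with 246 followed, 246 × 0.58 = 143 linkages fall to 246 × (0.58 − 0.352) = 56, among 246 × (1 − 0.352) = 159 people, so intervals widen. Disclosure drops out of the full-sample linkage model. For newly diagnosed participants this cannot be avoided, because the baseline interview precedes the HIV test.

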### Sample size justification and power analysis

The sampling scheme is stratified clustering with matched-pair sampling. Within each area, we pair matched clusters (villages) by distance to the HIV clinic and randomly assigned one village to be in the intervention arm. We have ensured that villages assigned to different study conditions are not within 4 km (1 h by foot) of each other to avoid possible discussions between different arms of participants.

We have powered the study to detect differences between the intervention and the standard-of-care for the primary outcome of HIV viral suppression (< 20 copies/ml) as well as intermediate outcomes: linkage to care and time to care, and, among those eligible for ART: time to and receipt of ART. Using census data, HBHCT acceptance rates from our own and other prior studies [22], HIV prevalence and prior knowledge of HIV status in this area from the recent prevalence survey [17], and estimating a 92% acceptance rate for enrollment of eligible participants into the study we calculated that the average cluster size (number of newly-diagnosed PLHIV per village who enroll in the study) will be 14 (range 8 to 37). In calculating the necessary clusters, type I error rate, desired power of tests, measure of effectiveness between the intervention and control group, cluster size, and coefficient of variation (k) or intraclass correlation coefficient are needed. We estimated viral suppression at 12-month follow-up among those eligible for ART at baseline to be 55% in the standard-of-care arm and 75% in the intervention arm. This estimate takes into account 12-month viral suppression success rates from SSA public sector ART programs [45, 81–84] and our own [23, 39] and others’ data on intermediate outcomes of linkage to care and ART initiation [22, 28]. With a type I error rate of 0.05 (two sided), average cluster size of 14, power of 80%, 12% difference in outcomes, and coefficient of variation of 0.24, we need 40 clusters after accounting for a 18% attrition rate for the follow-up. We expect that the 40 clusters will yield approximately 600 PLHIV participants across the two study arms.

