##### Two week CD4 results home visit

Two weeks after HBHCT, the control counselor will return to the participant’s home and provide them with their CD4 test results, and explain that they should take the CD4 results card with them when they present for HIV care. The counselor will also explain what the CD4 count means and if it indicates that they are eligible for ART, until the district adopts the MOH guidelines for immediate ART initiation, at which point they will be told they are eligible for ART regardless of CD4 test result. The two-week interval of return of CD4 results was the standard-of-care before “test and start” began to be adopted. With expansion of universal treatment, CD4 testing will no longer be a requirement for treatment initiation.

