#### Secondary outcome measures

Our main secondary outcome measures include HIV care linkage, ART initiation, and short-term retention in care (detailed below) collected through participant self-report at six and 12-month follow-up interviews, supplemented by clinic records and direct observation of participants’ HIV clinic cards and ART pill bottles where possible.
*Linkage and time to care* (six and 12 months, clinic records). We will assess linkage to care with data on: enrollment in an HIV clinic, having a second HIV clinic visit, and time from HIV testing to enrollment in care at an HIV clinic.
*ART initiation & time to initiation* (six and 12 months, clinic records). To assess receipt of HIV treatment we will determine if participants have been prescribed and have taken ART and the time from HIV testing to ART initiation. We will determine the percentage of participants eligible for ART (currently CD4 < 500 until the guidelines [8] to expand eligibility are implemented nationwide), who received antiretrovirals (ARVs) based on their CD4 count taken at the time of HBHCT, as well as the time from diagnosis to ART initiation. If possible, interviewers will directly observe the participant having ARVs at their home and review the patient’s HIV clinic record card to confirm self-reported data.
*Short-term retention in care* (six and 12 months, clinic records)*.* We will assess the following retention measures that have demonstrated the best discriminatory capacities for predicting viral suppression [45, 46]: a) missed visit count: number of missed visits accrued (count measure) based on scheduled visits determined by MOH clinical guidelines, b) visit adherence: proportion of kept visits/scheduled visits (kept + missed visits) (continuous measure, range = 0.0–1.0), and c) four-month visit constancy: number of four-month intervals with at least one kept visit (categorical measure, range = 0–3).

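### The 40-village calculation combines suppression rates for ART-eligible participants with a cluster size for everyone enrolled, so 80% power is not shown for the all-participant primary analysis

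*Protocol article*

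**What the plan says.** All references are to the protocol article.

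- **Planning rates** (Sample size justification and power analysis): "We estimated viral suppression at 12-month follow-up among those eligible for ART at baseline to be 55% in the standard-of-care arm", against 75% in the intervention arm.
- **Cluster size** (same section): "average cluster size (number of newly-diagnosed PLHIV per village who enroll in the study) will be 14". This counts everyone newly diagnosed who enrols, whatever their ART eligibility.
- **Power statement** (same section): two-sided 0.05, "power of 80%, 12% difference in outcomes, and coefficient of variation of 0.24", giving 40 villages after 18% attrition.
- **Primary outcome** (Data analysis approach): "To assess the primary outcome (the proportion of participants who are virally suppressed at 12-months", with no eligibility restriction. Hypothesis (a) in the Background is also unrestricted. The aims, the analysis section and the power section attach the eligibility condition to the ART outcomes only.
- **Entry** (Intervention trial): newly diagnosed, or known positive and never linked to care. There is no CD4 or ART-eligibility criterion.
- **Timing**: recruitment runs from November 2015 to August 2019, about 46 months. The threshold was CD4 < 500 at the start, and the Setting section expects universal eligibility during 2017.
- **Date of the eligibility change**: the Secondary outcome measures section has "currently CD4 < 500 until the guidelines [8] to expand eligibility are implemented nationwide". The control-arm section on the two-week visit has "until the district adopts the MOH guidelines for immediate ART initiation".

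**The concern.** The rates and the cluster size describe two different populations. While the CD4 threshold applied, some enrolled participants were not eligible for ART at baseline, and fewer of them would be expected to be suppressed at 12 months. If everyone is analysed, the planning rates and the 20-point difference are too high. If only the eligible are analysed, 14 per village is too many. The section gives neither an eligible share nor an all-enrolled suppression rate, so the reader cannot move from one population to the other.

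The 12% adds to the difficulty. It may be a slip, or it may be a diluted all-participant difference, but the section does not say which. At stake is the power quoted for the primary outcome, and so how a null result would be read.

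**Working it through.** **Inputs from the document.** Two-sided α = 0.05 and 80% power, so (1.960 + 0.842)² = 7.849. p0 = 0.55, p1 = 0.75, k = 0.24. Evaluable per village: m = 14 × 0.82 = 11.48. Matched pairs, 20 pairs.

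**Formula** (Hayes–Bennett, matched pairs). The article names no formula, so this choice is an assumption.

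V = p0(1−p0)/m + p1(1−p1)/m + k²(p0² + p1²)

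pairs = 2 + 7.849 × V / (p1−p0)²

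power at 20 pairs = Φ(√(18 × (p1−p0)²/V) − 1.960)

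**Step 1. Reproduce the plan's figure.**
V = 0.02156 + 0.01633 + 0.04982 = 0.08772.
Pairs = 2 + 7.849 × 0.08772/0.04 = 19.2, so 20 pairs = 40 villages, with 81.7% power.

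A second route also gives 40: m = 14, no added constant, and attrition applied to the village count (15.87/0.82 = 19.4, so 20 per arm). Both routes use eligible-only rates with the all-enrolled cluster size.

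**Step 2. Try the 12-point difference** (m = 11.48, k = 0.24).

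| Rates | Pairs (villages) for 80% | Power at 20 pairs |
|---|---|---|
| 0.55 v 0.67 | 48 (96) | 42% |
| 0.63 v 0.75 | 53 (106) | 39% |
| 0.33 v 0.45 (0.6 × each stated rate) | 35 (70) | 56% |

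None gives 40. A 12-point difference needs about 20 pairs only with a control rate near 15%, far from the stated rates.

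**Step 3. Match rates and population.** The eligible share f is not in the document. I assume f = 0.70–0.95 over the whole recruitment period.

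- *All enrolled, no effect in the ineligible*: p = f × 0.55 (or 0.75) + (1−f) × s, with the same assumed s in both arms, 0 to 0.20.
- *All enrolled, partial effect in the ineligible*: assumed 20% v 30% suppressed.
- *Eligible only*: 0.55 v 0.75 with m = 11.48 × f.

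Example, f = 0.8, s = 0.20: p0 = 0.44 + 0.04 = 0.48 and p1 = 0.60 + 0.04 = 0.64. V = 0.02174 + 0.02007 + 0.03686 = 0.07867. Power = Φ(√(18 × 0.0256/0.07867) − 1.960) = Φ(0.46) = 67.7%.

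| f | All enrolled, no effect (s = 0.20 to 0) | All enrolled, partial effect | Eligible only |
|---|---|---|---|
| 0.70 | 59–63% | 75% | 75% |
| 0.80 | 68–70% | 77% | 78% |
| 0.90 | 75–76% | 79.5% | 80% |
| 0.95 | 79% | 81% | 81% |

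With no effect in the ineligible, all-enrolled power reaches 80% once f is about 0.97.

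**Step 4. Is the range of f plausible?** Suppose recruitment is even over 46 months, 14 to 26 of them before universal eligibility (start or end of 2017), with 50–80% eligible in that time (assumed). Then f runs from (26/46) × 0.5 + 20/46 = 0.72 to (14/46) × 0.8 + 32/46 = 0.94. With s = 0, all-enrolled power is about 64–79%.

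**The case against.** The strongest reply is that the loss may be small. Universal eligibility was expected during 2017, so roughly 20 to 32 of the 46 recruitment months follow it and the whole-trial share could exceed 0.9. Many who enrolled earlier would become eligible before their 12-month visit. The intervention's two-week session also covers repeat CD4 testing for those not yet eligible, so some effect in that group is reasonable. All of this stands. It is why the partial-effect column is shown and why shares as low as 0.6 are not used for the main range. It limits the size of the problem but does not supply the missing population or rates.

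A second reply is that the 12% may already be the diluted difference. That does not rescue the figure: 33% v 45% has about 56% power with 20 pairs.

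A reader might infer that the trial is definitely underpowered, or needs more villages. The document does not support that, because it gives no eligible share and the answer runs from a large loss to almost none.

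A reader might also infer that someone with CD4 ≥ 500 who starts ART is lost from the ART outcomes altogether. The text does not go that far. The Secondary outcome measures section first records prescription, use and time to ART without restriction, and only then restricts the percentage to the eligible. A subset fixed at baseline is a legitimate choice, and analysing ART outcomes in everyone is a preference. What remains is that the two sections date the eligibility change differently. That is minor and does not touch primary power.

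**Conclusion.** The point holds as a mismatch between planning inputs and planned analysis. The stated 80% is reproduced only by putting eligible-only rates on an all-enrolled cluster size, and it is not shown for the all-participant primary outcome. The 12% in the power statement contradicts the section's own rates and cannot explain 40 villages at those rates.

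The size depends on an eligible share that the document does not give. Across the assumed shares, the shortfall from 80% runs from about 21 points to about 1 with no effect in the ineligible, and from about 5 points to none with a partial effect or in an eligible-only analysis. These figures hold k at 0.24 in every population and rest on the assumed suppression among the ineligible. This should be fixed, but it is not a reason to enlarge the trial.

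**What to change.** In the sample size section:

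1. Name all enrolled participants as the primary analysis population, in line with hypothesis (a).
2. Restate the planning suppression rates for that population, with the assumed eligible share before and after the policy change and the assumed suppression among those ineligible at baseline.
3. Correct or explain the 12% so that one difference is used throughout.
4. Restate the power that 40 villages give under those inputs, with a short range over the eligible share.

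As a separate minor edit, reconcile the two-week visit section (district adoption) with the Secondary outcome measures section (nationwide implementation), so that the ART-eligible analysis subset has one documented definition and date. An all-enrolled analysis of ART initiation may be added as supplementary.

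The cost is a revised paragraph and a recalculated power figure, probably somewhat below 80%. No participants, visits or data collection are added.
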